##### Patient-related outcomes

Patient-related primary outcomes will test non-inferiority in change scores on key clinical outcome measures from pre- to post- intervention when comparing those patients treated under the old model care compared to those treated under the new model of care. Furthermore, % patients treated adequately at each step of the Stepped Care Model will be measured by the number of patients discharged from the service by the treating clinician with outcome measures indicating reliable clinical change from pre- to post- intervention. The Clinical outcome measures include the Insomnia Severity Index (ISI) [34], Depression Anxiety and Stress Scale (DASS-21) [35], Kessler Psychological Distress Scale (K10) [36], and the EuroQol (EQ-5D-5 L) [37].

**Insomnia Severity Index** (ISI) is a 7-item self-report questionnaire assessing the nature, severity, and impact of insomnia over the past two weeks on a 5-point scale from 0 = no problem; 4 = very severe problem. The measure is widely used in the literature as well as clinically where a score of 11 is indicative of likely meeting criteria for an insomnia disorder in clinical trials and a change score greater than 8 is the minimally important difference to be considered ‘markedly improved’ or in remission [34, 38].

**Depression Anxiety and Stress Scale** (DASS-21) is a short version of a 42-item self-report instrument designed to measure three related negative emotional states: depression, anxiety and tension/stress over the past 7 days. Items are scored on a 3-point scale from 0 (did not apply to me at all) to 3 (applied to me very much, or most of the time). Total scores represent symptoms of distress in each of the domains in the ‘normal’, ‘mild’, ‘moderate’, ‘severe’ and ‘extremely severe’ relative to population norms [35].

**Kessler Psychological Distress Scale** (K10): The K10 is a 10-item self-report scale to assess symptoms over the past 4 weeks. Items are rated on a 5-point scale from 1 (none of the time) to 5 (all of the time). A score of less than 20 represents low psychological distress ‘likely to be mentally well’. Between 20 and 24 represents moderate distress ‘may have a mild mental disorder’ and between 25 and 29 represents high psychological distress ‘likely to have a moderate mental disorder’ [36].

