**EuroQol** (EQ-5D-5 L): The EQ-5D-5 L measures five dimensions of quality of life: mobility, self-care, usual activities, pain/discomfort and anxiety/depression. Each dimension has 5 levels: no problems, slight problems, moderate problems, severe problems, and extreme problems. The EQ VAS records the patient’s self-rated health on a vertical visual analogue scale where the endpoints are labelled ‘The best health you can image (100)’ and ‘The worst health you can image (0)’. The EuroQol also allows preliminary health economics evaluation by performing quality-adjusted life year calculations as a measure of cost-effectiveness of the intervention compared to standard care [37].

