##### Session Rating Scale (SRS)

The Session Rating Scale (SRS) is four-item visual analogue scale with each scale measured between 0 and 10 designed to assess key dimensions of effective therapeutic relationships and global satisfaction with treatment. The SRS is scored by summing score on each of the four scales with a total possible score of 40 [39].

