*How effective was the model of care in achieving its intended outcomes?*	**Effectiveness** – impact on outcomes and quality of life/economic outcomes	**Primary outcomes** *Service Access Measures* • Average number of occasions of Service within Sleep Psychology service under ‘old’ model compared to ‘new’ model of care • Percentage of new patient activity under ‘old’ model compared to ‘new’ model of care • Average wait-time to access a first appointment with Sleep Psychology from date of referral under ‘old’ model compared to ‘new’ model of care • Average time to discharge from first appointment to final appointment with Sleep Psychology under ‘old’ model compared to ‘new’ model of care • Percentage of patients discharged from psychology *Patient-related Outcomes* • Change scores on clinical outcome measures pre- to post- treatment on clinical outcome measures (ISI, DASS-21, K10 and EQ-5D-5 L) comparing patients treated under ‘old’ model versus ‘new’ model of care • % patients treated adequately at each level of Stepped Care • Differences in patient characteristics (age, sex, geographical location, presenting issue) between those who are adequately treated at each level of the new model of care (moderation analysis) *Economic Outcomes* • Quality-adjusted life year calculations as a measure of cost-effectiveness of the ‘new’ model of care compared to the ‘old’ model of standard care **Secondary outcomes** *Patient satisfaction* • Patient satisfaction measure (SRS) post- treatment comparing patients treated under ‘old’ model versus ‘new’ model of care *Patient satisfaction with digital intervention* • Patient reported ease of access to digital intervention • Acceptability and relatability of the online program/service provided (rated by patients), including: i. motivation to access online treatment (diversion from public hospital services for insomnia treatment) ii. understanding of intervention materials iv. perceived change in sleep problem • Differences in patient characteristics (age, sex, geographical location, presenting issue) between those who complete the digital intervention compared to those who do not complete	Significantly fewer occasions of service under new model of care Significantly greater % new patient appointments under new model Significantly shorter wait-time to first appointment under new model Significantly shorter time to discharge under new model Outcomes are non-inferior under new model of care; upper bound 95%CI on outcome measures is less than MCID MCID is achieved on outcome measures by > 80% patients at each level The ‘new’ model is more cost effective Patient reported satisfaction is non-inferior under new model of care; upper bound 95%CI is less than MCID > 90% patients report positive experiences	Patient qualitative and quantitative surveys Medical Record Patient registration system

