### Statistical analysis

The project will employ a mixed methods approach. Qualitative surveys for patients, multidisciplinary staff, and referrers was undertaken pre-service change to ascertain the acceptability of the digital therapy, as well as familiarity, access, confidence, and relatability of this treatment option [25]. Post-implementation surveys will also be undertaken on these same metrics. Quantitative data will be collected pre- and post-service change to ascertain treatment effectiveness in terms of clinical outcome measures, as well as service measures of interest such as patient flow, occasions of service and program engagement. Based on similar studies [40], and allowing for some incomplete data, we expect to have data for approximately 110 participants from each pre- and post- time period, resulting in a sample of 220 participants overall who will be suitable for the Direct to Psychology pathway. To assess wait times, participants will be categorised into four groups based on the time-period (pre/post implementation) and whether they met eligibility criteria for the Direct to Psychology pathway. Differences in wait times between the groups will be assessed using a one-way Analysis of Variance (ANOVA) and linear regression modelling. In a one-way ANOVA study, a sample of 220 participants, divided by 4 groups, achieves 80% power with a significance level of 0.05 to detect a moderate-large effect size (Cohen’s f) of 0.25 [41]. The effects of other variables of interest and potential confounders (patient characteristics, diagnosis,) will be tested in multivariable models. For differences in patient outcome measures pre- and post- intervention when comparing pre- and post- service change, the mean between-group difference and 95% confidence interval (CI) will be calculated. As this aspect of the evaluation is a non-inferiority trial (that is, we expect clinical outcomes to not be reduced due to the service change), the criteria adopted to determine non-inferiority will be if the upper bound 95%CI on each clinical outcome measure was less than the minimal clinical important difference (MCID). Quantitative data measuring pre- and post- service change outcomes on key indices of patient service satisfaction, service characteristics (e.g., occasions of service); as well as referrer and staff service satisfaction, and engagement with digital therapies, will be evaluated via univariate statistical tests where indicated such as independent samples t-test (or nonparametric equivalent), and categorical comparisons will be evaluated using Pearson’s chi-square. The distribution of outcome measures will be assessed, and appropriate transformations will be applied for use in modelling. Differences between group means will be tested using generalised linear regression modelling. Health related quality of life will be measured pre- and post- implementation using the EQ-5D-5 L. Population norms for EQ-5D-5 L Australia will be used to value the data set [42].

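### One upper-bound non-inferiority rule covers scales that run in opposite directions, with no sign convention stated; on scores as scaled it tests the wrong bound for one group of measures.

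*Protocol article*

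**What the plan says.** The Statistical analysis section of the Protocol article calls for a mean difference between the two service periods with a 95% CI on each patient outcome measure. It then says that the criterion for non-inferiority "will be if the upper bound 95%CI on each clinical outcome measure was less than the minimal clinical important difference (MCID").

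The Patient-related outcomes section lists the clinical measures as ISI, DASS-21, "Kessler Psychological Distress Scale (K10) [36], and the EuroQol" (EQ-5D-5L). Table 1, Effectiveness row, sets the same target for them: "Outcomes are non-inferior under new model of care; upper bound 95%CI on outcome measures is less than MCID". It sets it again for the SRS: "Patient reported satisfaction is non-inferior under new model of care; upper bound 95%CI is less than MCID".

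The article's own descriptions give the direction of the scales:
- **ISI, higher is worse:** "a score of 11 is indicative of likely meeting criteria for an insomnia disorder in clinical trials".
- **K10, higher is worse:** "A score of less than 20 represents low psychological distress".
- **DASS-21, higher is worse:** it is described as measuring negative emotional states.
- **EQ-5D-5L, higher is better:** the visual analogue scale has its top anchor at "The best health you can image (100"), and the valued responses feed the quality-adjusted life-year calculation.
- **SRS, higher is better:** "The SRS is scored by summing score on each of the four scales with a total possible score of 40". The direction is implied, since the scales rate the therapeutic relationship and satisfaction.

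The article does not say whether the difference is new minus old or old minus new, or that any score is reversed before the rule is applied.

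**The concern.** A test on the upper confidence bound rules out unacceptable harm only when a positive difference means that the new model is worse. Where a positive difference means better, the same test asks whether the new model is not better by more than the MCID. That is not non-inferiority.

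The hypotheses in Aims and objectives include non-inferior clinical outcomes and quality-of-life change. EQ-5D-5L is listed among the primary patient-related outcomes, and non-inferior SRS satisfaction is a secondary aim. If the rule is applied to the wrong side for these measures, a loss of quality of life or satisfaction could be reported as non-inferior and a real gain as a failure. If the direction is settled only at analysis, it could also be chosen after the results are known.

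**Working it through.** **Plan's own figure.** The article gives no operating characteristic for the non-inferiority rule. The only power figure in the section is for the wait-time ANOVA (220 participants, 4 groups, f = 0.25, stated 80%). A noncentral F calculation with noncentrality 220 × 0.25² = 13.75 gives 88.4%. The stated figure is conservative and plays no part below.

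**Step 1: which conventions make the rule correct.** The rule is: upper 95% bound < MCID.

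| Scoring | Contrast | ISI, DASS-21, K10 | EQ-5D-5L, SRS |
|---|---|---|---|
| As scaled (change = post minus pre) | new − old | correct | reversed |
| As scaled (change = post minus pre) | old − new | reversed | correct |
| Positive = better throughout | new − old | reversed | reversed |
| Positive = better throughout | old − new | correct | correct |

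Only the last row works for all five measures.

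**Step 2: size under new minus old, scores as scaled, for a higher-is-better measure.** Let d be the true new-minus-old difference, M the MCID and n the number per period.

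- From the article: n = 110 per period.
- Assumed, because the article gives neither for EQ-5D-5L: change SD 0.20 and M = 0.05 on the index. The subtraction order is also an assumption.
- SE = SD × √(2/n) = 0.20 × √(2/110) = 0.027.
- Rule as stated: P(pass) = Φ((M − d)/SE − 1.96).
- Mirrored rule (lower bound > −M): P(pass) = Φ((M + d)/SE − 1.96).

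| True d | Rule as stated | Mirrored rule |
|---|---|---|
| −0.10 (twice the MCID worse) | Φ(5.56 − 1.96) = Φ(3.60) = 0.9998 | Φ(−1.85 − 1.96) = Φ(−3.81), below 0.0001 |
| 0 | Φ(1.85 − 1.96) = Φ(−0.11) = 0.46 | 0.46 |
| +0.05 (better by the MCID) | Φ(0 − 1.96) = 0.025 | Φ(3.71 − 1.96) = Φ(1.75) = 0.96 |

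**Step 3: range.** Vary the SD from 0.15 to 0.25 and M from 0.03 to 0.08. A deficit of twice the MCID then passes the stated rule 76% to 100% of the time. The least extreme corner is SD 0.25 and M = 0.03: SE = 0.25 × √(2/110) = 0.0337, and Φ(0.09/0.0337 − 1.96) = Φ(0.71) = 0.76.

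**Step 4: the same check in SD units, which also serves for SRS.** SE = √(2/110) = 0.135 SD.

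| Margin | True difference | Rule as stated passes |
|---|---|---|
| 0.3 SD | worse by 0.5 SD | about 100% |
| 0.3 SD | better by 0.5 SD | 0.03% |
| 0.5 SD | worse by 0.5 SD | about 100% |
| 0.5 SD | better by 0.5 SD | 2.5% |
| 0.8 SD | better by 0.5 SD | 60.5% |

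The last line is a benefit smaller than the margin: it can pass.

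**The case against.** The strongest reply is that a coherent reading exists. If each change is scored as improvement and the difference is taken as old minus new, the contrast is the benefit lost under the new model. An upper limit on that loss is then the right test for the four clinical measures. SRS, compared post-treatment and already higher-is-better, fits without re-signing.

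Some of the article leans this way. The ISI description treats a change above 8 points as marked improvement, so positive means better there. The Statistical analysis section explains non-inferiority as an expectation that outcomes do not fall. Coding and contrast direction are also details that a condensed article may leave to a fuller document.

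Much of this stands. A reader might infer that no sign convention can make the rule correct, but the last row of the first table shows one that does. A reader might also infer that the plan as written is bound to certify harm. That does not follow either, because the article never says new minus old.

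The objection does not remove the point. The article states the decision rule itself, in the text and in two Table 1 targets, and applies it to scales of opposite direction without the convention that it needs. The ISI wording settles only half of that convention. With improvement scored positive and the usual new minus old, the rule is reversed for every measure.

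**Conclusion.** The concern holds in conditional form. One upper-bound criterion is fixed for ISI, DASS-21 and K10 and for EQ-5D-5L and SRS, with neither subtraction order nor re-signing stated. On scores as scaled, with one common order, it tests the wrong bound for one group: EQ-5D-5L and SRS under new minus old, or the three symptom scales under old minus new.

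That reversal follows from the scale directions and does not depend on any assumed SD or MCID. The probabilities (99.98%, 2.5%, and 76% to 100% over the range) rest on new minus old, an assumed SD and an assumed MCID.

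A reader might conclude that any better model fails. The calculation does not support that. Failure is near certain only once the benefit reaches the MCID (97.5% at exactly the MCID). Smaller benefits can pass, and at no true difference the stated and mirrored rules pass equally often.

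**What to change.** State the contrast and the bound in the Statistical analysis section and in both Table 1 targets (clinical outcomes and satisfaction), before the outcome data are analysed. Either of two equivalent forms will do:

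1. Take new minus old throughout. For ISI, DASS-21 and K10 (change as post minus pre), require the upper 95% bound to be below +MCID. For EQ-5D-5L (change as post minus pre) and SRS (post-treatment score), require the lower 95% bound to be above −MCID.
2. Score every measure so that positive means better, take old minus new, and keep the upper-bound rule.

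The second needs the fewest edits and matches the sign that the article already uses for ISI change. The cost is a sentence or two in the text and a matching edit to two table targets. No new data, patients or analyses are needed.

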### Secondary outcomes

#### Patient satisfaction

To test for non-inferiority in satisfaction with the provided service measured when comparing those patients treated under the old model care compared to those treated under the new model of care, a feedback informed treatment tool will be utilised.

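### Satisfaction (SRS) is to be judged non-inferior by a confidence bound in the Measures section and Table 1, but the Statistical analysis section assigns patient satisfaction to difference tests

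*Protocol article*

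**What the plan says.** **Objective.** Under Secondary outcomes, the Patient satisfaction section gives the purpose as "To test for non-inferiority in satisfaction with the provided service", comparing patients under the old and new models. The tool is the SRS; its own section says "The SRS is scored by summing score on each of the four scales with a total possible score of 40".

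**Criterion.** The Effectiveness row of Table 1 (RE-AIM) gives the target: "Patient reported satisfaction is non-inferior under new model of care; upper bound 95%CI is less than MCID".

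**Analysis.** The Statistical analysis section states a non-inferiority rule of the same kind, but for a narrower set of outcomes. The criterion is whether the "upper bound 95%CI on each clinical outcome measure was less than the minimal clinical important difference (MCID"). The Patient-related outcomes section identifies those measures: "The Clinical outcome measures include the Insomnia Severity Index (ISI) [34], Depression Anxiety and Stress Scale (DASS-21"), followed by the K10 and EQ-5D-5L. The SRS is not among them. The next sentence of the Statistical analysis section begins "Quantitative data measuring pre- and post- service change outcomes on key indices of patient service satisfaction", adds service characteristics, referrer and staff satisfaction and engagement with digital therapies, and says that these "will be evaluated via univariate statistical tests where indicated such as independent samples t-test (or nonparametric equivalent").

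**The concern.** The section that tells the analyst what to do separates satisfaction from the non-inferiority rule and groups it with outcomes such as occasions of service, for which Table 1 wants a significant difference. A difference test asks whether zero is compatible with the data. Non-inferiority asks whether a loss as large as the margin can be excluded. A non-significant test does not exclude such a loss, and a significant one may reflect a loss too small to matter.

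The fallback adds a second problem. Satisfaction totals with a ceiling at 40 may well be skewed, which is when an analyst turns to the nonparametric test. That test gives no bound on the mean difference to set against an MCID.

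At stake is the support for one of the article's stated expectations: the abstract anticipates that patient experience, as well as outcomes, will be non-inferior.

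**Working it through.** **1. The three statements side by side**

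| Place in the protocol article | Question for satisfaction | Decision tool |
|---|---|---|
| Secondary outcomes, Patient satisfaction | Non-inferiority | Not given there |
| Table 1, Effectiveness, Standard/Target | Non-inferiority | 95% CI bound against MCID |
| Statistical analysis | Difference between periods | t-test or nonparametric equivalent |

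The third row does not deliver what the first two ask for.

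**2. Direction of the bound**

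Table 1 refers to the upper bound. That suits an old-minus-new difference on a score where higher is better. If higher SRS totals mean more satisfaction, as the description suggests, and the difference is taken as new minus old, the unfavourable side is the lower bound. The article does not say which way the SRS difference is taken.

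**3. The plan's own figures**

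The article gives no power figure, SD or MCID value for the SRS. Its only power statement concerns the wait-time ANOVA (220 participants, four groups, f = 0.25, 80%). Noncentrality 220 × 0.25² = 13.75 gives 88.4%, so that statement is conservative, and it has no bearing here.

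**4. What would follow if non-significance were read as success**

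The article does not state this rule for the SRS; the calculation shows only how far apart the two readings could lie.

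- From the article: about 110 per period; 95% CI.
- Assumed: equal groups, normal scores, margin m of 0.3, 0.4 or 0.5 SD, true loss equal to m. The smaller n are illustrative; the article gives no SRS return rate.

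Noncentrality: δ = m√(n/2). At n = 110, √55 = 7.416, so δ = 2.225, 2.966 and 3.708. With 218 df the two-sided 5% critical value is about 1.971. The chance of a non-significant result is approximately Φ(1.971 − δ), that is Φ(−0.254), Φ(−0.995) and Φ(−1.737). Exact noncentral-t values:

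| n per period | m = 0.3 SD | m = 0.4 SD | m = 0.5 SD |
|---|---|---|---|
| 110 | 0.399 | 0.160 | 0.042 |
| 80 | 0.529 | 0.290 | 0.118 |
| 55 | 0.655 | 0.453 | 0.262 |
| 30 | 0.792 | 0.668 | 0.522 |
| 15 | 0.875 | 0.815 | 0.738 |

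Under the confidence-bound rule the chance of passing at a true loss equal to the margin is 0.025 in every cell.

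**5. Is the confidence-bound rule workable?**

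With no true difference and 110 per period, the chance of passing is 0.601, 0.840 and 0.958 for the three margins. For 80% power, n per period = 2(1.960 + 0.842)²/m², which gives 175, 99 and 63. With m = 0.4 SD the chance falls to 0.331 at 30 per period.

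**The case against.** The strongest reply is that the decision rule is already in print. Table 1 gives satisfaction a confidence-bound criterion, and the Statistical analysis section does not withdraw it. The wording there is permissive and covers a batch of outcomes. An independent-samples t-test comes with a mean difference and a 95% CI, and the same section says that group means will be compared by generalised linear regression, which also yields an interval. The sentence does not name the SRS and could refer partly to survey items. Most of this stands. It means that a careful analyst who reads both places could reach the right analysis, and that only the nonparametric fallback cannot supply the bound. It does not remove the mismatch: the Statistical analysis section limits the non-inferiority rule to a list without the SRS, then names patient satisfaction and gives it other tests. The SRS remains the most natural reading of that phrase.

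A reader might go further and infer that missing questionnaires would make the satisfaction claim easier to pass. That requires non-significance to count as success. The article sets such a target in the Implementation row of Table 1, for comparisons between intervention staff, but for satisfaction it sets a confidence bound. The documents therefore do not support the stronger reading, and the rates in step 4 are conditional on it.

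Nor is the absence of a numerical SRS margin a fault in itself; a condensed article may leave that to the full protocol or analysis plan.

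**Conclusion.** The inconsistency is real and lies in the current text. The stated analysis of patient satisfaction does not match its stated objective or its criterion in Table 1, and the bound named there is the wrong one if the difference is taken as new minus old on a score where higher is better.

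It is a minor correction. The SRS is a secondary outcome, a suitable criterion is already printed, and the named t-test or the regression model can produce the interval. If non-significance were taken as success, the false-pass rate at 110 per period would be about 40%, 16% or 4% rather than 2.5%, and higher with fewer responders. Those figures rest on assumed margins of 0.3 to 0.5 SD and on a success rule that the article does not adopt for the SRS. They show why the wording should be settled, not what the trial will do.

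**What to change.** In the Statistical analysis section, take the SRS out of the t-test sentence and extend the confidence-bound rule to it. Report the mean between-period difference with a 95% CI, using a bootstrap interval if the scores are skewed. State the direction of the difference and judge non-inferiority on the unfavourable-side bound (the lower bound of new minus old, if higher SRS means more satisfied) against a prespecified SRS margin. Word the Table 1 target to match.

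If no margin can be justified, drop the non-inferiority claim for satisfaction in the Patient satisfaction section and Table 1, and report the difference with its CI.

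The cost is a sentence or two and a justified margin; no new data are needed. The downside is that the claim becomes harder to make when few patients return the SRS.

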### Design and setting

This project will employ a single-site, multi-phase, mixed-methods approach to evaluate the implementation of the new model of care into the Sleep Psychology service in a tertiary public hospital, embedded within the RE-AIM implementation evaluation framework [19, 20, 22]. Reporting will align with the Standards for intervention Reporting Implementation Studies (STaRI) framework [23]. Patient, service-level and implementation outcomes will be evaluated by comparing patients attending the service from 1 January 2021 until 30 June 2023 as a pre-measure (old model of care) to patients attending the service from implementation of the model from 1 July 2023 to 31 December 2024 as a post-measure (new model of care). This project has received ethics approval via the low and negligible risk pathway with a waiver of informed consent with the Darling Downs Human Research Ethics Committee (HREC 2022 QTDD 88350). Figure 1 outlines the study flow.

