#### Primary outcomes

##### Service access measures

Access measures include new patient activity for the sleep psychology service, and time from referral to treatment commencement and discharge within the sleep psychology service when comparing patients treated under the old model of care compared to those treated under the new model of care. Number of clinical occasions of service will be collected for the sleep psychology service and the medical service and compared for those attending under the old model of care compared to those attending under the new model of care. 

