### Implementation and evaluation – RE-AIM

To measure the impact of our service change on both patient and service/organisational level outcomes, the evaluation is outlined below with according to the RE-AIM framework (see Table 1).

**Table 1 Tab1:** RE-AIM evaluation framework

Evaluation Question	RE-AIM Domain	Indicator/Measure	Standard/Target	Data Source
*Did patients access care as expected under the new model of care?*	**Reach – The absolute number**,** proportion**,** and representativeness of individuals who are willing** **to participate**	• Percentage of patients agreeing to digital compared to those offered • Patient-reported reasons for declining digital intervention • Percentage of patients referred Direct to Psychology who remain on this pathway • Differences in patient characteristics (age, sex, geographical location, presenting issue) between those agreeing to digital compared to those declining • Number of patients and patient characteristics (age, sex, geographical location, presenting issue) of those assigned to each treatment level • Differences in patient characteristics (age, sex, geographical location, presenting issue) between those referred Direct to Psychology compared to those referred via the standard pathway • Time to start the online program from date of prescription for those assigned to digital intervention • % digital intervention sessions completed for those assigned to digital intervention	> 80% patients offered digital intervention accept digital < 20% patients are referred back to standard care > 80% patients commence within 4 weeks > 80% patients complete digital intervention	Patient qualitative and quantitative surveys Medical Record Patient registration system

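### Occasions of service, a primary outcome with a significance target, is given univariate tests between two non-randomised periods, and no adjusted analysis is tied to it or named as deciding

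*Protocol article*

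**What the plan says.** **Status of the outcome.** The protocol article lists it among the primary service access measures: "Number of clinical occasions of service will be collected for the sleep psychology service and the medical service". Table 1 (RE-AIM, Effectiveness) states the contrast as "Average number of occasions of Service within Sleep Psychology service under ‘old’ model compared to ‘new’ model of care" and sets the target "Significantly fewer occasions of service under new model of care".

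**Design.** Under Design and setting, the evaluation rests on "comparing patients attending the service from 1 January 2021 until 30 June 2023 as a pre-measure (old model of care") set against patients seen from "implementation of the model from 1 July 2023 to 31 December 2024 as a post-measure (new model of care"). These periods last 30 and 18 months. Nothing is randomised.

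**Analysis.** Three sentences in Statistical analysis could bear on this outcome:

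1. After the wait-time ANOVA and its power statement, potential confounders (patient characteristics and diagnosis) are to be examined in multivariable models. No outcome is named.
2. After the non-inferiority text, a list that includes "service characteristics (e.g., occasions of service") "will be evaluated via univariate statistical tests where indicated such as independent samples t-test (or nonparametric equivalent"). This is the only sentence that names the outcome.
3. Next, after a sentence on transformations for modelling, group means are to be compared by generalised linear regression. Neither an outcome nor a covariate is named.

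**Descriptive comparisons.** Table 1 plans comparisons such as "Differences in patient characteristics (age, sex, geographical location, presenting issue) between those referred Direct to Psychology compared to those referred via the standard pathway", and others by treatment level, digital uptake and adequacy of treatment. It lists none between the old and new cohorts.

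**The concern.** A univariate test between two calendar cohorts estimates the effect of the new model plus any difference in who was seen. Case-mix plausibly drives this outcome. Levels 3 and 4 add strategies for sleep or mental health comorbidities, and the number of Level 3 sessions depends on what the patient needs. Opening a direct route for insomnia referrals could also alter the referral stream.

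If the later cohort holds more straightforward patients, mean occasions fall even though care for any given patient is unchanged, and the significance target can be met for that reason alone. A shift the other way could hide a real saving. Adjusting wait times would not protect this claim, which bears directly on the hypothesis of less resource-intensive care. The wait-time analysis does separate patients by eligibility for the direct pathway, but no such step is tied to occasions of service.

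**Working it through.** **The plan's own figure.** The only power statement is for wait times: 220 patients in 4 groups, f = 0.25, alpha 0.05, power 80%. A noncentral F with noncentrality 220 × 0.25² = 13.75 and 3 and 216 degrees of freedom gives 88.4%, so 80% is conservative. It does not concern occasions of service, for which no figure is given, and nothing below depends on it.

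**Inputs**
- From the documents: about 110 patients per period (Statistical analysis) and a two-sided test at 0.05, hence 2.5% in the direction favouring the new model.
- Assumed: two patient types; negative binomial counts with dispersion k = 4, so variance = m + m²/4; mean occasions 4 (uncomplicated) and 8 (complex), with 5 and 8 as an alternative; uncomplicated share 50% in the old period; no effect of the model.

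**Formulas.** With uncomplicated share p and type means m₁ and m₂:
- cohort mean = p·m₁ + (1−p)·m₂
- cohort variance = p·(m₁ + m₁²/4) + (1−p)·(m₂ + m₂²/4) + p(1−p)(m₂−m₁)²
- d = difference in cohort means ÷ √(average of the two variances)
- false-success rate ≈ P(Z > 1.96 − d√(110/2))

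**Means 4 and 8.** The type variances are 4 + 16/4 = 8 and 8 + 64/4 = 24. Old period: mean 6.0; variance 0.5·8 + 0.5·24 + 0.25·16 = 20.

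| New share | New mean | Fall | New variance | d | d√55 | Rate |
|---|---|---|---|---|---|---|
| 60% | 5.6 | 0.4 | 18.24 | 0.091 | 0.68 | 10.0% |
| 65% | 5.4 | 0.6 | 17.24 | 0.139 | 1.03 | 17.6% |
| 70% | 5.2 | 0.8 | 16.16 | 0.188 | 1.40 | 28.6% |

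**Means 5 and 8.** The type variances are 11.25 and 24. Old period: mean 6.5, variance 19.875. For 60%, 65% and 70% the falls are 0.3, 0.45 and 0.6, d is 0.068, 0.104 and 0.140, and the rates are 7.3%, 11.7% and 17.8%.

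**Simulation of the same settings**

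| Uncomplicated share in new period | 50% | 60% | 65% | 70% |
|---|---|---|---|---|
| Means 4 and 8, t-test | 2.6% | 9.7% | 17.9% | 28.4% |
| Means 4 and 8, Mann-Whitney | 2.5% | 9.5% | 17.3% | 27.1% |
| Means 4 and 8, adjusted for patient type | 2.7% | 2.5% | 2.5% | 3.0% |
| Means 5 and 8, unadjusted | 2.2% | 7.8% | 11.7% | 18.1% |
| Means 5 and 8, adjusted for patient type | 1.9% | 2.8% | 2.6% | 2.5% |

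Simulation and formula agree. The nonparametric option gives no protection. Adjustment for the driver of case-mix, when it is measured, brings the rate back to about nominal.

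**The case against.** A reader might infer that an unadjusted t-test is the whole plan for this outcome. The text does not support that. The tests are offered where indicated, with a nonparametric alternative. The outcome is an average compared between two groups, so the general regression sentence can be read to cover it. Only the position of the confounder sentence, not its wording, ties it to wait times. This stands, and it limits the point to what is left unassigned and undecided.

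A reader might also infer that a case-mix shift would go unseen because Table 1 has no old-versus-new comparison. That goes too far. Table 1 lists RE-AIM indicators, not every planned table, and eligibility for the direct pathway is to be classified in both periods for wait times. Nor do the documents show that a shift has occurred or will occur: the same inclusion rule spans both periods, physician triage continues, and the pathway also admits patients with suboptimal adherence to sleep apnoea treatment.

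The error rates can be challenged too. The figure of 110 per period describes patients suitable for the direct pathway, which excludes highly comorbid patients, so a 50% complex share is only illustrative. The resource hypothesis also draws on cost-effectiveness, service costs against revenue, and occasions per staffing resource.

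Finally, covariate lists and model details are often left to a statistical analysis plan. That answers a complaint about missing detail. It does not answer the fact that the article names a method for this primary outcome, and that method cannot deal with case-mix. On the generous reading, an unadjusted and an adjusted test serve one target, with no rule for which decides.

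**Conclusion.** The point holds in limited form. For a primary outcome judged by statistical significance between two non-randomised periods, the only method explicitly assigned is univariate. The adjusted analyses mentioned nearby are neither linked to the outcome nor given the deciding role. With no effect of the model and the assumed shifts, the chance of wrongly declaring a reduction is about 8% to 18% (means 5 and 8) or about 10% to 28% (means 4 and 8), against 2.5%. The direction of the problem is certain if case-mix moves towards simpler patients. Its size is not, because the documents give neither the spread of occasions of service nor any change in case-mix. This should be corrected before analysis, but it is not evidence that the comparison will be biased.

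**What to change.** State in Statistical analysis that the deciding test for occasions of service is the period effect from a generalised linear count model (for example negative binomial). Adjust it for prespecified pre-treatment characteristics: age, sex, geographical location, presenting issue or diagnosis, eligibility for the direct pathway, and baseline ISI. Do not adjust for treatment level, which is part of the new model and would remove some of its effect. Keep the univariate test as descriptive, and report these characteristics for the old and new cohorts side by side.

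The cost is small: a few sentences, one model and one table, using a model class that the section already names and variables that the protocol already lists or uses. There are two limits. Baseline values will be missing for some patients, perhaps more often in the earlier cohort, so the handling must be stated in advance. Adjustment also deals only with measured case-mix; secular change between the periods remains and should be acknowledged when the result is interpreted.
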